### **Secondary objective**

Outcome variables include Individual Clinical Response (ICR, 0~25: sum of the top 5 domains on a 5-point Likert scale), Gait analysis results (improved, no change, worsened), Stair climb/descent (time and quality of improvement), Sleep diary (sum of the number of overnight awakenings, average duration of overnight awakenings, and duration of time for initial sleep onset at bedtime), and Stooling survey results. For univariate analyses, similar statistical tests will be used as ones used for the primary objective, depending on the data type of the outcome for comparing two study periods. For multivariate analyses, mixed effect models (linear for continuous outcomes and non-linear such as multinomial logistic regression for categorical outcomes and Poisson (or Negative Binomial regression model, if over-dispersion is apparent) for count outcomes) will be used using 2-4 different time points (pre-observation, 8, 36 week treatment, post-observation periods) as within subject factor. Covariates such as sex and age will be considered in multivariate models if they are found to be statistically significant in changes of outcomes. Sub-scale analyses will be conducted if changes in the composite score are found to be statistically significant or are reached to a clinically meaningful boundary. We expect to have full data without any missing for all outcomes. However, in case of missing data, two imputation methods, i) last observation forward, ii) multiple imputation assuming missing at random, will be considered.

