### **6.0 Study-Wide Number of Subjects**

Twenty (20) subjects will be enrolled in this pilot study. Individuals who withdraw before Week +8 will be replaced.

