| Sanfilippo Behavior Rating Scale                       |           | X                               | X                 |                                                              | X                                | X                                      |
| Non-communicating Children's Pain Checklist-Revised    |           | X                               | X                 |                                                              | X                                | X                                      |
| Parent reported outcomes (PROMIS) d         |           | X                               | X                 |                                                              | X                                | X                                      |
| Seizure - parent assessment x 1 week                   |           | X h                  | X                 |                                                              | X                                | X                                      |
| Movement - parent assessment x 1 week                  |           | X h                  | X                 |                                                              | X                                | X                                      |
| Individual Clinical Response                           |           | X                               | X                 |                                                              | X                                | X                                      |
| Gait assessment                                        |           | X                               | X                 |                                                              | X                                |                                        |
| Vineland-III                                           |           | X                               |                   |                                                              | X                                |                                        |
| Stair climb                                            |           | X                               | X                 |                                                              | X                                |                                        |

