## 12.2 Analysis

### **Primary objective**

Outcome variables include AEs/tolerability, 2 most bothersome symptoms, and multi-domain responders index (MDRI) as described in section 9.1. Binary AEs such as hospitalization ( $\geq 1$ ) will be summarized using frequencies/rates by the two period (pre-observation, treatment). The multiple event such as the total number of seizures will be summarized using median with the inter-quartile range (IRQ). For testing changes between the two periods, the McNemar's test (binary event) or Wilcoxon Signed Rank test (multiple events and MDRI) will be used. For continuous outcomes such as laboratory results, a paired t-test and a repeated measures ANOVA will be used. Residual analyses will be conducted to check the model assumption. If it violates assumption, Friedman test (nonparametric) will be used instead.

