### **Exploratory objective**

Explanatory outcomes include stool microbiome and Vineland 3. The similar analyses as ones for primary and secondary objectives will be carried out based on data types.

Analyses will be conducted using the programs of SAS v9.4 (SAS Institute, Cary, NC). All tests will be two-tailed and a P value less than 0.05 will be considered statistically significant. The primary outcome will be tested at the 5% significance level. Secondary, exploratory and sensitivity analyses will not be adjusted for multiplicity. Therefore, the results will be interpreted with caution and discussed with recognition of inflated family-wise type I error rate.

Descriptive statistics will be provided on all study data collected from the total cohort (N=20) from the entry to the trial to the completion of 44 weeks follow-up continuous variables will be summarized as numbers of observed and missing values, mean, standard deviation, median, minimum and maximum. Categorical variables will be described as frequencies and percentages.

Any post-hoc, exploratory analyses or deviations which were not identified in this data analysis plan but are completed to support the planned analyses will be clearly identified and the reasons documented.

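### The only model named for categorical secondary outcomes ignores order; used for the three-level gait rating in 20 children, it would cost some power and could be inestimable if an outer level is rare

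*Protocol*

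**What the plan says.** Protocol Section 12.2 (Secondary objective) lists the secondary outcomes, among them "Gait analysis results (improved, no change, worsened"). Section 9.1 gives the same three levels, rated by a physical therapist.

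The section then sets two routes of analysis.

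- **Univariate:** "similar statistical tests will be used as ones used for the primary objective, depending on the data type of the outcome". The tests for the primary objective include an order-respecting one: "Wilcoxon Signed Rank test (multiple events and MDRI) will be used".
- **Multivariate:** mixed-effect models, linear for continuous outcomes, "non-linear such as multinomial logistic regression for categorical outcomes", and Poisson or negative binomial for counts, "using 2-4 different time points (pre-observation, 8, 36 week treatment, post-observation periods) as within subject factor". Sex and age may enter as covariates.

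No ordinal model is named anywhere in the protocol. On size, Section 6.0 says "Twenty (20) subjects will be enrolled in this pilot study". On testing, Section 12.2 says "All tests will be two-tailed and a P value less than 0.05 will be considered statistically significant". In the schedule of Section 10.2, the row "Gait assessment" is marked at Week -8, Day +1 and Week +36 only.

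**The concern.** Worse, unchanged and better form an ordered scale, and gait is the only secondary outcome that Section 12.2 lists with category labels. A baseline-category multinomial model treats the labels as unordered. It estimates two separate period effects where the question is whether ratings shift in one direction.

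Three gait visits give each child at most one rating for the observational period and one for the treatment period, about 40 ratings in all. If no child falls in an outer level in one period, the corresponding log-odds is infinite and the model gives no usable period effect.

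At stake is the multivariate analysis of a secondary endpoint. A model switch made after such a failure would be a deviation that Section 12.2 itself requires to be identified and explained. It is simpler to name a suitable model now.

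**Working it through.** **1. The plan's own figure.** Section 12.3 states no power for gait. Its nearest figure is a 95% margin of error of 13% to 18% for a binary event at proportions of 5% to 15% with n = 20.

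- Plain Wald, 1.96 × √(p(1−p)/20): 9.6% and 15.7%.
- Wald plus the continuity correction 1/40: 12.1% and about 18%.
- Clopper-Pearson: 12.4% and 17.3%.
- Wilson with continuity correction: 13.3% and 17.5%.

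The corrected and exact forms match the stated range within about one point. Section 12.3 also says that feasibility set the sample size, so there is no power claim to contradict.

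**2. Parameters against data.** With period, sex and age, the multinomial model has 2 intercepts + 2 period effects + 4 covariate effects = 8 fixed parameters, plus random effects. The cumulative-logit model has 2 thresholds + 1 period effect + 2 covariate effects = 5, plus one variance. Both draw on about 20 × 2 = 40 ratings.

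**3. Empty levels.** If a share p of children is rated improved in a period, the chance that none of 20 is so rated is (1−p)^20. For p = 5% (assumed) this is 0.95^20 = 36%. For p = 20% it is 0.80^20 = 1%.

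**4. Cost of the second degree of freedom.** At equal non-centrality, compare a 1-df chi-square test (critical value 3.84) with a 2-df test (5.99), both at 0.05.

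| Non-centrality | 1 df | 2 df | Gap (points) |
|---|---|---|---|
| 2.06 | 30% | 23.1% | 6.9 |
| 3.84 | 50% | 40.1% | 9.9 |
| 4.90 | 60% | 49.5% | 10.5 |
| 10.51 | 90% | 83.5% | 6.5 |

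**5. Marginal simulation.** Twenty children, two periods, a proportional-odds shift, 2,000 datasets per scenario. Assumed base levels were 33/34/33, 20/60/20, 30/60/10, 10/80/10 and 15/80/5, with log-odds shifts of 0.8 to 2.0. The ordinal model gained 1 to 11 points by likelihood-ratio test. Example at 20/60/20 with odds ratio exp(1.6): multinomial 65%, cumulative logit 74%, Wilcoxon signed rank 68%, with an empty cell in 39% of datasets.

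**6. Mixed-model simulation.** As in step 5, with a random child intercept (SD 1) and 300 datasets per scenario; simulation error is about 3 points. Base levels run from worst to best and apply to a child whose random effect is zero. Not estimable means an empty period-by-level cell or a diverging coefficient.

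| Base levels, shift | Multinomial not estimable | Ordinal coefficient diverged | LR power, multinomial / ordinal | Wald power, multinomial / ordinal |
|---|---|---|---|---|
| 33/34/33, 1.3 | 8% | 0% | 45% / 53% | 34% / 53% |
| 20/60/20, 1.3 | 22% | 0% | 47% / 55% | 28% / 54% |
| 20/60/20, 1.8 | 38% | 2% | 70% / 78% | 46% / 77% |
| 15/80/5, 1.3 | 49% | 7% | 42% / 48% | 2% / 32% |
| 15/80/5, 1.8 | 60% | 15% | 65% / 70% | 11% / 51% |

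The gaps are 5 to 8 points by likelihood ratio and 18 to 41 by Wald test, because near-separation inflates the Wald standard errors. With no effect, the likelihood-ratio tests rejected in 6%, 9% and 8% of datasets (multinomial) and 3%, 6% and 9% (ordinal) at 20/60/20, 15/80/5 and 33/34/33. Neither holds 5% exactly at this size, which is a reason to keep an exact test available.

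**The case against.** The strongest reply is that the protocol commits to less than a quick reading suggests. The multinomial model is introduced as an example for categorical outcomes in general. It is not assigned to gait, and an ordinal model is not excluded. The choice of link for one secondary outcome is often left to the SAP, which is not at hand. The univariate route already leaves the Wilcoxon signed-rank test open, and with two change periods a paired test is a natural analysis of gait. The multinomial model also avoids the proportional-odds assumption, which the simulations above grant to the ordinal model.

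Much of this stands. A reader might infer that gait is to be analysed by multinomial regression and that the analysis will usually fail. The text supports neither: the first turns an example into a commitment, and the second depends on level frequencies that the protocol does not give.

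A reader might also infer a fixed loss of roughly 10 to 15 points. That is what a 2-df Stuart-Maxwell test shows against a 1-df test on -1/0/+1 scores in four assumed scenarios (12% against 22%, 36% against 49%, 57% against 72%, 71% against 84%). Stuart-Maxwell is only a stand-in for the mixed model, and the gap changes with the assumed frequencies and with the test.

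What remains is that the one model named for categorical outcomes is a poor fit for the one outcome listed with ordered levels, and no alternative is offered.

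**Conclusion.** The point holds as a minor improvement. If the named model were used for gait, it would discard the order and use two degrees of freedom where one suffices. Under an effect, it would be inestimable in about 8% of datasets with equal thirds and up to about 60% with levels 15/80/5.

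Under proportional odds the power loss against a cumulative-logit model is about 1 to 11 points with likelihood-ratio tests and 18 to 41 points with Wald tests; the protocol does not say which test applies. These ranges rest on assumed level frequencies, log-odds shifts of 0.8 to 2.0 and a random-intercept SD of 0 or 1. The documents fix only the 20 children, the gait visits, the three levels and the two-sided 0.05 level.

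The signed-rank test's power advantage is small in the worked example (68% against 65%). Its main merit is that it respects the order and does not break down when a level is empty. The primary endpoints are unaffected, and secondary results are already to be read with caution and without multiplicity adjustment.

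**What to change.** In Section 12.2 (Secondary objective), add that:

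- ordered categorical outcomes such as gait will be modelled by a cumulative-logit mixed model with a random child effect;
- the paired univariate comparison will be the exact Wilcoxon signed-rank test on ratings scored -1/0/+1 (treatment-period rating minus observational-period rating);
- the same test is the fallback if a level is empty or the model does not converge.

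Apply this to stair-climb quality only if it is recorded in ordered categories; Section 10.17 does not define any.

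Keep the model as well as the rank test. Replacing the model outright would give up the covariates and time points that the section wants from the multivariate analysis. The cost is wording and a proportional-odds assumption, which 20 children can hardly test. No visit, measurement or participant is added.

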### 3.0 Objectives

The primary objectives of the study are to:

1. Evaluate the safety and tolerability of anakinra in children age  $\geq 4$  years with MPS III, defined by the incidence of treatment-emergent adverse events and abnormal laboratory values, and number of subjects withdrawn due to intolerability (e.g. unable to administer SC injection to subject, worsening behaviors).
2. Evaluate the effect of anakinra on a multi-domain responder index (MDRI) as a means to determine need for dose escalation. Due to the inherent heterogeneity of disease presentation, the MDRI will measure change tailored to patient-specific symptoms. MDRI change will inform dose-finding by reflecting lack of change in clinical outcome. The MDRI will be composed of the following:
  - Sanfilippo Behavior Rating Scale (SBRS)
  - Child Sleep Health Questionnaire (CSHQ)
  - Autism Parenting Stress Index (APSI)
  - PROMIS Fatigue - Parent Proxy Custom Short Form
  - Seizures – parent reported frequency, duration, and severity
  - Movement disorder (e.g. dystonia, chorea, etc.) – parent reported frequency, duration, and severity
  - Non-communicating Children's Pain Checklist-Revised (NCCPC-R)

The secondary objectives of the study are to evaluate the effect of anakinra on:

- Individual Clinical Response (ICR) – 5 most impactful clinical problems reported by the caregiver
- Gait
- Stair climb/descent
- Sleep Diary (1-week recall)
- Sanfilippo Syndrome Stool Habit Questionnaire

The exploratory objectives of the study are to evaluate the effect of anakinra on:

- ☐ Stool microbiome
- ☐ Vineland Adaptive Behavior Scales, Third Edition (VABS-III)

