## 4.0 Background

Sanfilippo syndrome, or mucopolysaccharidosis type III (MPS III), is a genetic disorder of metabolism, associated with insufficient production of a lysosomal enzyme crucial for degradation of heparan sulfate. As a consequence, buildup of heparan sulfate causes progressive, irreversible neurodegeneration. There are four variants of MPS III, distinguished by the lysosomal enzyme deficiency: Heparan-N-sulfatase (MPS IIIA),  $\alpha$ -N-Acetylglucosaminidase (MPS IIIB), AcetylCoA:N-acetyltransferase (MPS IIIC) and N-Acetylglucosamine 6-sulfatase (MPS IIID). MPS IIIA and MPS IIIB are the most common subtypes.

Unlike other types of MPS which involve considerable somatic complications, the most significant aspect of MPS III is neurodegeneration which manifests in stages of developmental disruption and decline, defined by Cleary and Wraith. Their 3-stage model involves: 1) developmental delay in cognition and language before age 3-4 years, 2) temper tantrums, hyperactivity, aggression, sleep disorder, and a further loss of cognitive and language function from age 3-4 years to age 8-10 years, and 3) loss of motor function, feeding difficulties, and seizures from age 8-10 years. Recent work has determined that there is a loss of about 15 IQ points per year in children with MPS IIIA who are younger than 6 years and that they do not surpass a mental age equivalent of 30 months. The advancing disease causes the neurobehavioral profile to meet diagnostic criteria for autism^3, and to overlap with Kluver-Bucy syndrome. A study of patients with both MPS IIIA and IIIB in several European countries found comparable patterns of disease progression in the groups, with delayed language development and cognitive decline, as well as disruptive behavior, particularly in children diagnosed before age 5.

The neurobehavioral symptoms associated with MPS III are highly disruptive and distressing to families, have a significant impact on the quality of life for the patient and family, and likely interfere with adjunctive therapeutic attempts at supporting the child. However, despite the universal acknowledgment that these neurobehavioral symptoms are a prominent concern for MPS III, these symptoms have not been the therapeutic target.

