| Whole Blood                                            |           | X                               | X                 |                                                              | X                                | X                                      |
| Anakinra e                                  |           |                                 |                   |                                                              |                                  | X (week 8 and 16 only)                 |
| Adverse events f                            |           | X                               | X                 |                                                              | X                                | X                                      |
| Contact for study follow up g               |           | Required every 4 weeks ± 7 days |                   |                                                              |                                  |                                        |

a If sponsor discontinues the study at any time, or a subject is discontinued from the study after week +8 and before week +44, an early termination visit will be done. Early termination visit procedures will be the same as for the week +44 visit.

b All procedures/intervention/surgery due to underlying MPS III will be recorded after informed consent is obtained, until week 44 or the Early Termination visit. If a subject is discontinued from the study prematurely, all procedures/intervention/surgery due to underlying MPS III will be recorded at the Early Termination visit.

c All medications (prescription, over-the-counter and herbal) and nutritional supplements taken 30 days prior to Screening and throughout the study should be documented.

d PROMIS surveys are the Autism Parenting Stress Index (APSI) and a customized Parent Proxy Fatigue – Short Form.

e The same injection site should not be used 2 days in a row, and should be rotated between the four injection sites (upper thigh, upper back of arm, abdomen or buttocks). Dose will be escalated at week 8 and 16, or decreased at any time, per protocol described in Section 27.7 Dosing.

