## **14.0 Withdrawal of Subjects**

Subjects will be encouraged to complete the study; however, they may voluntarily withdraw at any time. If a subject is withdrawn prior to study completion, attempts will be made to schedule and conduct an Early Termination visit for medical assessment. If a subject cannot be contacted after 5 telephone calls and 3 letters/emails, they will be considered lost to follow-up.

Subjects who discontinue study medication (e.g. due to non-compliance, AEs, etc.) will be asked to remain in the study for follow-up per the study schedule to preserve the ability to perform an intent to-treat (ITT) analysis. If a subject or their legal guardian (as applicable) withdraws consent to participate in the study, attempts will be made to obtain permission to record survival and adverse event (malignancy, hospitalization for infection) data at the Week +44 study point.

Study drug will be discontinued in any subject meeting the following criteria for drug-induced liver injury:

- ☐ ALT or AST > 8x upper limit of normal (ULN)
- ☐ ALT or AST > 5x ULN for more than 2 weeks
- ☐ ALT or AST >3x ULN and (total bilirubin >2x ULN or INR > 1.5)
- ☐ ALT or AST >3x ULN with the appearance of fatigue, nausea, vomiting, right upper quadrant pain or tenderness, fever, rash, and/or eosinophilia (>5%)

Management of suspected drug-induced liver injury will be consistent with the FDA Guidance for Industry Drug-Induced Liver Injury: Premarketing Clinical Evaluation. Specifically, an increase of ALT or AST of >3x ULN will be followed by repeat testing within 48-72 hours of ALT, AST, alkaline phosphatase, and total bilirubin level. There will be inquiry made about symptoms. If symptoms persist or repeat testing shows ALT or AST >3x ULN close observation to determine whether the abnormalities are improving or worsening will be initiated as follows:

- ☐ Repeating liver enzyme and serum bilirubin tests two or three times weekly. Frequency of retesting can decrease to once a week or less if abnormalities stabilize or the trial drug has been discontinued and the subject is asymptomatic.
- ☐ Obtaining a more detailed history of symptoms and prior or concurrent diseases.
- ☐ Obtaining a history of concomitant drug use (including nonprescription medications and herbal and dietary supplement preparations), alcohol use, recreational drug use, and special diets.

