### **27.7 Dosing**

In this study anakinra subcutaneous (SC) will be administered at a dose level of 100 mg SC once daily. Anakinra will be administered every other day in patients who have severe renal insufficiency or end stage renal disease (defined as creatinine clearance < 30 mL/min as estimated from serum creatinine levels).

**Dose will be increased to 200 mg SC once daily**, with a maximum dose limit of 8 mg/kg/day, at **Week +8** if the change in at least one of the two most bothersome outcomes selected by the parents/guardians at the Day 1 visit has not improved by  $\geq$  the MCID as defined in Section 9.1. If the MCID is not achieved after 8 weeks on maximum trial dose of 200mg (max dose 8 mg/kg/day), **treatment with anakinra may be discontinued after a review and discussion between the study PI and subject's parent(s) of their child's individual results from all study outcome measures.**

**Dose will be increased to 200 mg SC once daily**, with a maximum dose limit of 8 mg/kg/day, at **Week +16** if the change in at least one of the two most bothersome outcomes selected by the parents/guardians at the Day +1 visit have worsened by  $\geq$  the MCID as defined in Section 9.1 between week +8 and week +16, after an improvement from Day +1 to week +8. If the MCID is not achieved after 8 weeks on maximum trial dose of 200mg (max dose 8 mg/kg/day), **treatment with anakinra may be discontinued after a review and discussion between the study PI and subject's parent(s) of their child's individual results from all study outcome measures.**

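### Section 12.2 names last observation carried forward as a missing-data method; in this single-arm trial of a progressive disease it can hide decline and should be removed

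*Protocol*

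**What the plan says.** The missing-data text is in Section 12.2 of the protocol, under the secondary objective, but it speaks of all outcomes. It opens with "We expect to have full data without any missing for all outcomes" and continues that, if data are missing, "i) last observation forward, ii) multiple imputation assuming missing at random, will be considered". No order between the two methods is given. The same paragraph plans mixed-effects models with time as a within-subject factor.

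Other sections bear on how data could go missing:

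- Section 4.0 describes the disease course: "buildup of heparan sulfate causes progressive, irreversible neurodegeneration".
- Section 3.0 counts, as a tolerability outcome, the "number of subjects withdrawn due to intolerability (e.g. unable to administer SC injection to subject, worsening behaviors").
- Section 14.0 says that children who stop the drug "will be asked to remain in the study for follow-up per the study schedule".
- Section 10.2, footnote a, says that if "a subject is discontinued from the study after week +8 and before week +44, an early termination visit will be done", with the same procedures as Week +44.
- Section 6.0 replaces those who withdraw before Week +8.
- Section 12.1 bases the primary analyses on the safety population, which is everyone who received any treatment. The protocol-compliant population, used for sensitivity, requires attendance at every scheduled visit.

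**The concern.** LOCF assumes that a child's score stays where it was last seen. In a randomised trial a control arm may partly offset that assumption. Here there is none: Section 9.1 defines the endpoints as change within the child, over 8 weeks of treatment against 8 weeks of observation, and from the start of treatment to Week +36. If the disease advances after the last recorded value, the frozen value hides that decline and the on-treatment change looks better than it was. The filled value also enters the test as if it had been measured, so the standard error is too small.

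This is not a detail left for a later document. The protocol itself names the method, in a section that describes itself as the data analysis plan. What is at stake is the reading of the Week +8 and Week +36 changes. At Week +44 the effect differs: carrying Week +36 forward sets the change after drug withdrawal to zero, which would hide the very effect the last 8 weeks are meant to show. That error does not favour the drug.

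**Working it through.** **The plan's own figure.** The only computed figure is the precision statement in Section 12.3. For n = 20, t(0.975, 19)/√20 = 0.468 SD, in line with the stated half SD. For proportions of 5% and 15%, a continuity-corrected Wald interval gives 12.1% and 18.2%, close to the stated 13% to 18%. These figures make no allowance for missing data, and the LOCF point does not depend on them.

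**Which value LOCF would carry (Section 10.2 schedule)**

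| Outcome | Scheduled at | Part of early termination visit? | Value carried to Week +36 |
|---|---|---|---|
| Gait, stair climb | Week -8, Day +1, Week +36 | No | Day +1, before treatment effect: change = 0 |
| Vineland | Week -8, Week +36 | No | Week -8: change = 0 |
| Questionnaires (sleep, behaviour, pain, stress, fatigue) | Week -8, Day +1, Weeks +8, +16, +36, +44 | Yes, after Week +8 | Early termination value if obtained; otherwise up to Week +16, bridging 36 - 16 = 20 weeks |

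For a treated child who leaves before Week +8, the last scheduled questionnaire value is Day +1 and footnote a offers no termination visit. Replacement under Section 6.0 does not remove the child from the safety population. LOCF then sets the treatment-period change to 0. Because the contrast subtracts the observation-period change, a child who worsened by x during observation would be scored as x better on treatment. A child who improved by x would be scored as x worse. All this assumes that pre-treatment values may be carried; the protocol sets no limit.

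**Size, simple form (assumed inputs).** Shift in the mean = (fraction filled) × (unrecorded further decline). With 5 of 20 filled and 0.5 SD of decline: 0.25 × 0.5 = 0.125 SD. With 0.25 to 1 SD of decline: 0.06 to 0.25 SD. The protocol gives neither a dropout rate nor a decline rate for these scales.

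**Standard error (same assumed 5 of 20).** Suppose 15 observed changes have mean 0 and SD s. Their standard error is s/√15 = 0.258s. Adding five zeros gives √(14s²/(19 × 20)) = 0.192s, about 26% smaller with no added information.

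**Direction, by simulation (assumed inputs).** No drug effect, score SD 1, within-child correlation 0.7, 10 to 30% missing at Week +36, LOCF from Week +16, decline of 0 to 0.25 SD per 8 weeks. Negative means toward benefit.

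| Why the child leaves | LOCF bias (SD) | MAR imputation bias (SD) |
|---|---|---|
| Unrelated to outcome, no decline | about 0 | about 0 |
| Unrelated to outcome, decline 0.05 to 0.25 per 8 weeks | -0.01 to -0.19 | about 0 |
| Worsening recorded at last visit, decline 0 to 0.10 | +0.14 to +0.04 | about 0 |
| Worsening recorded at last visit, decline 0.25 | +0.01 to -0.05 | about 0 |
| Worsening after the last visit, never recorded | -0.14 to -0.46 | -0.11 to -0.30 |

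The second row can be checked by hand: bias = -(fraction missing) × (decline per 8 weeks) × 20/8. At the extremes, 0.1 × 0.05 × 2.5 = 0.0125 and 0.3 × 0.25 × 2.5 = 0.1875.

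**The case against.** A reader might infer that LOCF biases this trial toward benefit as a matter of course. The documents do not support that. The early termination visit repeats the main questionnaires, and if it captures the worsening that prompted departure, LOCF carries a bad value forward and the bias can run against the drug.

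A reader might also infer that non-responders will be a main source of missing data. They should not be: under Section 27.7, failure to reach the MCID may stop the drug, and Section 14.0 asks such children to stay on the visit schedule.

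Three further points have force. Section 4.0 supports progression in general but gives no decline rate over 8 or 36 weeks for these scales. LOCF is only one of two methods to be considered, and an analysis plan not shown may drop it. Removing it does not cure everything, since MAR imputation is also biased if worsening goes unrecorded.

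What stands is narrower. The early termination visit omits gait, stair climb and the Vineland, does not cover departures before Week +8, and under Sections 10.20 and 14.0 is something that will be attempted. Where it gives no value, LOCF has nothing sound to carry. A bias whose sign depends on whether the worsening was recorded is itself a reason not to use the method. The stated sensitivity population does not help, because it excludes children who missed visits.

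**Conclusion.** The point holds in a limited form. The protocol names LOCF in a setting where it can hide decline and overstates precision. It fixes the change at zero for gait, stair climb and the Vineland in any child without Week +36 data, and for the questionnaires in treated children who leave before Week +8, if pre-treatment values may be carried. For the other Week +36 values the direction is open: under the assumed inputs it ran from 0.46 SD toward benefit to 0.14 SD against the drug. Every size given here is illustrative, because it rests on assumed dropout, decline and correlation. If data are complete, as Section 12.2 expects, nothing changes.

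**What to change.** In Section 12.2:

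1. Delete last observation carried forward.
2. Make the mixed model already planned, fitted to all observed visits, the main analysis of the longitudinal outcomes. The time points now listed there do not mention Week +16, which should be included where the outcome is measured.
3. Keep multiple imputation under MAR as supporting analysis.
4. Add one sensitivity analysis that applies a fixed unfavourable shift, set in advance, to the imputed values of children who left the study for worsening or intolerance. This is needed because both the mixed model and the imputation rely on MAR, which fails if the worsening was never recorded.

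The cost is a change of wording and one extra run. Intervals may be slightly wider than under LOCF. No visit or procedure changes.
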